### Statistical analysis

Intention-to-treat principles will be followed in statistical analyses. Categorical variables will be expressed as counts with percentages. Normally distributed data will be presented as the means with standard deviations (SDs), while nonnormally distributed data will be reported as medians with interquartile ranges (IQRs). Comparisons of significant differences between groups will be performed by Student’s *t*-test for continuous variables with normal distributions, the nonparametric Kruskal–Wallis test for nonnormally distributed data, and the Pearson chi-square test for categorical data. With regard to repeated measurements throughout gestation (e.g., weight), the results will be presented separately for each timepoint. For binary endpoints, risk ratios and risk differences with 95% confidence intervals will be calculated by binomial regression. All analyses will be performed unadjusted and adjusted for appropriate baseline values.

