**Discussion:**

To date, this is the first randomised controlled trial aimed to evaluate the protective effect of an individualised nutritional intervention against GDM based on a logistic regression prediction model. Eligibility is not limited to obese women or singleton pregnancies, as in previous studies. This pragmatic trial is expected to provide valuable information on early screening and effective GDM prevention methods.

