Previous studies have indicated that lifestyle modification strategies addressing healthy eating and/or physical activity can effectively prevent type 2 diabetes mellitus in nonpregnant populations [9]. Nutritional patterns in early pregnancy have been suggested to be associated with GDM development [10]. Counselling and behavioural interventions have been reported to be effective in limiting excess gestational weight gain (GWG), which is associated with a decreased risk of GDM [11–13]. As a first-line strategy for GDM management, nutritional interventions mainly involve a dietician’s personalised diet prescription in accordance with nutritional intake guidelines during pregnancy [14]. A prospective study with a small sample size (*n* = 50) suggested that GWG in obese women (body mass index (BMI) ≥ 30 kg/m^2^) can be reduced through the implementation of 10-h dietary consultations (gain of 6.6 kg in the intervention group vs gain of 13.3 kg in the control group, *p* = 0.002), thus reducing the incidence of GDM (0% in the intervention group vs 10% in the control group) [15]. The conclusions of an RCT conducted in nine European countries with 150 participants with BMI ≥ 29 kg/m^2^ support the application of early healthy eating interventions in obese pregnant women, as evidenced by lower GWG and lower fasting glucose in the intervention group [16]. Another prospective randomised controlled trial with a larger sample size (*n* = 269) conducted in Finland showed that obese pregnant women (BMI ≥ 30 kg/m^2^) who received individualised counselling on physical activity, diet, and weight gain control from trained nurses and dieticians had a lower prevalence of GDM (13.9% in the intervention group vs 21.6% in the control group, *p* = 0.044) [17]. Nevertheless, the UPBEAT study from the UK indicated that behavioural intervention in obese pregnant women (BMI ≥ 30 kg/m^2^) was not adequate to prevent GDM (25.0% in the intervention group vs 26.0% in the standard care group, *p* = 0.68) [18]. Currently, the level of evidence on whether nutritional intervention can prevent GDM is considered to be low to very low since it is challenging to implement these interventions and monitor measurement error and diet complexity under free-living circumstances [19, 20]. On the other hand, previous studies mostly targeted obese pregnant women with singleton pregnancies or those with a previous history of GDM [14, 15, 17]. As stated in a study conducted in America, nearly one-third of GDM patients (29.3%) were underweight or normal weight [21]. Currently, it remains unproven whether nutritional intervention can prevent GDM in a more general population, such as normal-weight women, women with multiple pregnancies or women with fasting blood glucose equal to or higher than 5.1 mmol/L in the early conception period. Therefore, modifiable risk factors and pragmatic interventions need to be identified.

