### Participants

Women in early pregnancy who attend the antenatal clinics of three research centres will be identified by the GDM risk prediction model mentioned above. According to the multiple logistic regression model we previously established, the predictive probability of GDM development in our study population will be calculated with the formula 1/[1 + exp.(−β)], in which β equals (− 14.2334 + (0.0681*age) + (0.5005* blood triglyceride level in the first trimester, mmol/L) + (2.8165* fasting blood glucose level in the first trimester, mmol/L) + (1.1062*family history of diabetes in first-degree relatives) + (1.6925* HbA1c in the first trimester, %) + (0.4349*multiple pregnancy) + (2.6181* previous history of GDM). The area under the receiver operating characteristic curve of this model was 0.77 (95% CI 0.76–0.78). The optimum threshold probability was 0.13 with 59% sensitivity and 82% specificity when the Youden index was set at 0.41 [24]. Consequently, pregnant women with a calculated risk probability of GDM equal to or higher than 0.13 in the first trimester are considered high risk. Among them, pregnant women at less than 14 gestational weeks who are able to understand and provide informed consent and are ready to receive antenatal care and deliver at one of the research centres will be eligible to participate in our study.

We will exclude individuals if they have been diagnosed with the following disorders: pre-pregnancy essential hypertension, renal disease, HIV, hepatitis B or C, cardiac disease, thalassemia, cystic fibrosis, systemic lupus erythematosus or any other autoimmune disease, thyroid disease requiring medication, pregestational diabetes (including patients diagnosed with diabetes before conception; fasting blood glucose ≥7.0 mmol/L or HbA1c ≥ 6.5% in the first trimester; typical hyperglycaemic symptoms or hyperglycaemic crisis with optional blood glucose ≥11.1 mmol/L), or current prescription of medicines, such as metformin and glucocorticoids, that affect blood glucose values.

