### Recruitment and randomisation

The research staff will verbally inform eligible pregnant women that the hospital is currently conducting a multicentre clinical trial to identify better preventive strategies for GDM and that they are eligible to participate. If they fully understand and are willing to join the study, they will meet the research staff in person at the hospital, sign an informed consent form and officially participate in the project prior to 14 gestational weeks. Baseline data, including sociodemographic characteristics and medical and maternal history, will be collected by standardised questionnaires. Each participant will be given a sequential study number by research staff. Subsequently, their basic information will be entered into an internet-based and password-protected clinical research management system (ResMan Research Manager, supported by West China Hospital, Sichuan University, China), which will automatically generate a research code and randomly allocate participants to the intervention group or the control group at a ratio of 1:1. The research assistants responsible for data collection, biostatisticians and data analysts will be masked to study group allocation. Given the nature of the intervention, the participants and investigators will be aware of the assignment.

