*Neonatal-* Infant sex; gestational age at birth (based on estimated date of delivery); Apgar score; birth length; birth weight assessed for macrosomia (≥ 4000 g), low birth weight (< 2500 g), large for gestational age (LGA), and small for gestational age (SGA); preterm birth (PTB, < 37 weeks); shoulder dystocia; bone fracture; bronchial plexus injury; neonatal hypoglycaemia; neonatal respiratory distress; jaundice for which treatment is warranted; neonatal intensive care unit (NICU) admission; congenital anomalies; livebirth; miscarriage (< 20 weeks); still birth (≥ 20 weeks); and neonatal death (within the first 28 days after delivery) will be assessed. LGA and SGA will be defined as a birth weight above the 90th or below the 10th percentiles of newborns of the same gestational age and sex, respectively, in accordance with the INTERGROWTH-21st growth standards published in 2014 [39]. Neonatal hypoglycaemia refers to venous glucose levels lower than 2.6 mmol/L within the first 48 h after birth.

*Dietary-* Daily average energy intake, macronutrient intake (proteins, fats, carbohydrates), vitamin intake (vitamin A, vitamin D, vitamin E, vitamin C, vitamin B1, vitamin B2, niacin, and folic acid), mineral intake (calcium, phosphorus, iron, and zinc), and dietary fibre intake (g) will be assessed.

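### Multiple pregnancies are enrolled on purpose, but the only tests named for neonatal outcomes assume independent observations; if infants are the rows, some of these tests run above their nominal 5%

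*Protocol article*

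**What the plan says.** **Who is enrolled.** The abstract's Discussion states: "Eligibility is not limited to obese women or singleton pregnancies, as in previous studies". The Background lists groups in whom prevention is unproven, "such as normal-weight women, women with multiple pregnancies or women with fasting blood glucose equal to or higher than 5.1 mmol/L". In Participants, the eligibility score carries the term "0.4349*multiple pregnancy", a positive weight. The list that begins "We will exclude individuals if they have been diagnosed with the following disorders" does not contain multiple pregnancy.

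**What is randomised.** Under Recruitment and randomisation, the system will "randomly allocate participants to the intervention group or the control group at a ratio of 1:1". The participant is the woman, so her infants always fall in the same arm.

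**What is measured on infants.** The neonatal secondary outcomes include Apgar score, birth length, neonatal hypoglycaemia and "neonatal intensive care unit (NICU) admission". Birth weight is classed as macrosomia, low birth weight, large for gestational age and small for gestational age.

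**How groups are compared.** Statistical analysis gives one rule for all between-group comparisons: Student's t-test for normal data, Kruskal–Wallis for non-normal data, "and the Pearson chi-square test for categorical data". Risk ratios and risk differences come from binomial regression. Everything is run both unadjusted and adjusted for baseline values. Repeated measurements over gestation are to be shown by timepoint. Siblings are not mentioned, and the article has no cluster term, robust variance, one-value-per-mother rule or restriction to singletons.

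**The concern.** Each named method treats its rows as independent. Two infants of one mother are not: they share the mother, the arm and the fact of being twins, and for preterm birth they share the outcome itself. Where twins have much higher event rates than singletons, a chance imbalance of a few twin pregnancies between arms shifts the comparison by two infants at a time, while the naive standard error counts each infant separately.

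Objective and hypothesis extends the trial's hypothesis to offspring perinatal outcomes. Intervals that are too narrow and p-values that are too small would bear on that part of the claim.

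**Working it through.** The article gives no figure for the neonatal analyses, so there is none to reproduce. The check asks how far a naive per-infant test departs from 5% when there is no treatment effect.

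**Inputs**
- About 225 mothers per arm (450 expected completers, Sample size calculation). The number cancels from the ratio below.
- Twin share *t* = 3%, 5%, 10% of mothers, with all multiples taken as twins. Assumption.
- Event rates *ps* (singletons) and *pt* (each twin), and within-pair correlation *ρ*. Assumptions.

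**Formulas**
- Infant event rate: p = [(1−t)·ps + 2t·pt] / (1+t).
- Singleton part: A = (1−t)·[ps(1−ps) + (ps−p)²].
- Twin part: B = t·[2·pt(1−pt)(1+ρ) + 4(pt−p)²].
- Ratio of true to naive variance: R = (A+B) / [(1+t)·p(1−p)].
- Actual type I error of a nominal 5% test: 2·[1 − Φ(1.96/√R)].

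When ps = pt, R reduces to the design effect 1 + 2tρ/(1+t).

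**Worked example: preterm birth counted per infant, 5% vs 50%, ρ = 1, t = 3%**
- p = (0.97×0.05 + 0.06×0.5)/1.03 = 0.0762
- A = 0.97×(0.0475 + 0.0007) = 0.0467
- B = 0.03×(1.000 + 0.718) = 0.0516
- R = 0.0983/(1.03×0.0704) = 1.36
- Type I error = 2·[1 − Φ(1.96/1.164)] = 9.2%

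**Results (type I error at t = 3% / 5% / 10%)**

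| Outcome, assumed rates singleton vs twin | ρ | Type I error |
|---|---|---|
| Macrosomia, 8% vs 1% | 0.5 | 5.1 / 5.1 / 5.3% |
| Large for gestational age, 12% vs 2% | 0.5 | 5.1 / 5.2 / 5.4% |
| Same rate in both | 0.5 | 5.3 / 5.6 / 6.1% |
| Moderately commoner in twins, 10% vs 30% | 0.5 | 6.0 / 6.5 / 7.4% |
| Low birth weight, 4% vs 50% | 0 | 7.1 / 7.5 / 7.8% |
| Low birth weight, 4% vs 50% | 0.5 | 8.5 / 9.4 / 10.3% |
| Preterm birth per infant, 5% vs 30% | 1 | 8.0 / 9.3 / 11.3% |
| Preterm birth per infant, 5% vs 50% | 1 | 9.2 / 10.6 / 12.3% |

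The low-birth-weight row with ρ = 0 is still inflated because both twins share the raised rate. Within-pair correlation adds to that.

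**Simulation check.** 20,000 null trials were run with 225 mothers per arm, rates 5% vs 50% and correlation 0.5 on an underlying normal scale. The naive chi-square test rejected in 4.7% of trials with no twins and in 7.4 / 8.1 / 9.3% at 3 / 5 / 10% twins. On the binary scale that correlation is about 1/3 within twin pairs ((2/π)·arcsin 0.5), and the formula then gives 7.6 / 8.3 / 9.1%. For a continuous outcome with twins assumed 1.7 SD lower, the t-test rejected in 5.0% with no twins and in 6.7 / 7.5 / 8.9%.

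**The case against.** **The article never says that infants are the rows.** It names tests by type of data, randomises and counts women, and follows intention to treat. One value per mother, such as any NICU admission, fits every sentence, and an analysis plan that is not shown may settle it. A reader might infer that the plan prescribes treating siblings as independent. The text does not support that, so the point has to be conditional. It is still more than missing detail: the section positively names tests that do not suit infant-level data in the population the trial chose. The per-mother reading also needs a rule for turning two birth weights or two Apgar scores into one.

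**The largest figures are a worst case.** A reader might infer that false positives roughly double across the neonatal outcomes. The 9–12% applies to preterm birth, and only if one delivery is entered twice. For several listed outcomes the inflation is negligible.

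**Heavy enrichment with twins is not shown.** The coefficient of 0.4349 is an odds ratio of about 1.54. It moves the score as much as 0.4349/2.8165 ≈ 0.15 mmol/L of fasting glucose. The article gives no twin share.

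**Adjustment is already allowed.** Baseline adjustment is planned and number of foetuses is collected, so plurality may be included. But it is not named, the unadjusted analysis is reported too, and a covariate does not remove the remaining sibling correlation from the standard errors.

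**Maternal outcomes are not touched.** Gestational weight gain and mode of birth are listed as maternal, with one value per woman, so they raise no sibling problem.

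**Conclusion.** The point holds in a limited, conditional form. Followed literally on infant rows, the named tests give standard errors that are too small for some neonatal secondary outcomes. At 3–10% twin pregnancies the actual level of a nominal 5% test is about:
- 5–6% where rates do not differ by plurality or are lower in twins;
- 6–10% for infant-level outcomes that are commoner in twins;
- 9–12% for preterm birth at 5% vs 50%, if each sibling is counted.

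The twin share, event rates and sibling correlations are assumptions, because the article states none of them. The direction does not depend on their exact values, provided siblings are positively correlated. The primary outcome and the maternal outcomes have one value per woman and are unaffected. The matter is worth correcting before analysis, but it does not threaten the trial's main conclusion.

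**What to change.** In Statistical analysis:
- State the unit of analysis for the neonatal outcomes.
- Analyse infant-level outcomes by binomial regression (binary) or linear regression (continuous), using GEE or cluster-robust standard errors with the mother as the cluster.
- Include number of foetuses, already recorded under Data collection, as a covariate in the adjusted analysis.
- Analyse preterm birth and gestational age at birth once per pregnancy.

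No change is needed for gestational weight gain, mode of birth or the primary outcome. The cost is a few lines of text and code, and slightly wider intervals for some neonatal outcomes. No new data or change of design is required.

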#### Data management and confidentiality

All paper versions of the materials will be stored in a designated locked cabinet, while electronic data will be saved in the password-secured ResMan Research Manager system. Double data entry will be performed by a full-time trained clerk and a supervisor. Original information from pen-and-paper baseline questionnaires and 3-day food records will be collected and processed under the instructions of clinicians and nutritionists of the study. Data entered incorrectly will be examined and corrected by the supervisor after confirmation with the participants or their obstetric records. Any revision of the original data will be tracked in detail.

Participants’ personal information or any data will remain anonymous and be kept securely throughout the study. Unauthorized access to the database or disclosure is not allowed at any trial centre. All staff members are responsible for strict confidentiality of information at all times.

#### Data monitoring and auditing

The Trial Steering Committee (TSC) is composed of CZ, [name], [name], [name], [name] and [name], who will be responsible for study oversight and overall conduct. A Data Monitoring Committee (DMC) consisting of four members will be set up for on-site audits and data quality control. The DMC will be independent from the sponsor, and there will be no competing interests. Two audits for each centre will be performed: at the midpoint and at the end of the trial. Emphasis will be placed on whether recruitment, data collection, nutritional intervention and follow-ups are conducted and updated according to the protocol. Moreover, the quality of self-administered 3-day food records will be comprehensively assessed for both completeness and precision. Validity of original data source will be verified by randomly selected samples. A formal report will be created, which will provide useful instructions not only for problem solving in due time but also for statistical analyses in the future. No interim analysis has been planned for the primary or secondary outcomes. In terms of adverse events (AEs), diet interventions are safe considering that evidence on related harms was very limited in general [11], but any unintended occurrence of AEs associated with the study interventions will be reported to the TSC and recorded in detail by the staff member.

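### Adverse events outside the listed outcomes are to be recorded only when linked to the intervention, which leaves them almost without a control-arm comparator

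*Protocol article*

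**What the plan says.** Adverse events are dealt with in one sentence of the protocol article, at the end of Data monitoring and auditing. It begins from the premise that "diet interventions are safe considering that evidence on related harms was very limited in general" and then provides that "any unintended occurrence of AEs associated with the study interventions will be reported to the TSC and recorded in detail by the staff member". It does not say who decides whether an event is associated, by what criteria, or whether any other event is written down.

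The same section describes two committees. The Trial Steering Committee (TSC), which receives these reports, is the body "who will be responsible for study oversight and overall conduct". The other is described thus: "A Data Monitoring Committee (DMC) consisting of four members will be set up for on-site audits and data quality control". Of it the article says, "The DMC will be independent from the sponsor, and there will be no competing interests".

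On masking, Recruitment and randomisation says that "the participants and investigators will be aware of the assignment", and also: "The research assistants responsible for data collection, biostatisticians and data analysts will be masked to study group allocation".

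Separately, Secondary outcomes lists many maternal, fetal and neonatal events that bear on safety. Data collection says these are taken from inpatient records and confirmed by research clinicians.

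**The concern.** A between-arm comparison of adverse events needs the same recording rule in both arms. A rule that admits an event only if it is associated with the intervention is not the same rule in practice when one arm does not receive that intervention. A control woman can have the same event as an intervention woman and not qualify, because there is no counselling to associate it with.

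In the intervention arm the count depends on attribution. The trial is open-label, and the adverse-event sentence itself presumes the intervention to be safe, which makes attributing an event to it less likely.

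At stake is the adverse-event table for anything not already on the outcome list. Purely as illustrations, this might be symptomatic hypoglycaemia, ketosis, or distress about dietary restriction. If such events were recorded under this rule, a count in the intervention arm beside almost nothing in the control arm could not be read as excess harm. A low count in both arms could not be read as reassurance.

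**Working it through.** The article gives no adverse-event rate or count, so there is no figure to reproduce. The check sets the provisions side by side.

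1. **Which events the rule admits.** Data monitoring and auditing names only events associated with the study interventions. No other adverse-event provision appears in the article.

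2. **What each arm receives.** Under Dietary intervention, the intervention arm has three individual sessions with a dietician before the glucose tolerance test. Under Standard care, the control arm completes five food records, is not scheduled to see a study dietician, and may seek ordinary dietary advice. Food recording is therefore the only study procedure a control event could be associated with.

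3. **What the rule does to the counts.** Let *n* be the number of women per arm, *r* the true rate of some event, taken as equal in both arms, and *a* the fraction of events judged associated with the intervention. Then:
   - recorded in the intervention arm = *n* × *r* × *a*(I)
   - recorded in the control arm = *n* × *r* × *a*(C)
   - ratio of recorded counts = *a*(I) / *a*(C)

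   The true rate cancels. With *a*(C) close to zero (step 2), the control count is close to zero whatever *r* is. The intervention count lies anywhere between 0 and *n* × *r*, according to *a*(I). The recorded comparison reflects attribution, not incidence. With relatedness kept as a separate field, *a* = 1 in both arms at the recording stage and the ratio estimates the true one.

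4. **Who sets *a*(I).** The sentence mentions only an unspecified member of staff. Investigators know the allocation. Under Dietary intervention, follow-up staff remind women of dietician visits, so they would in practice know it too. The assistants who collect data are masked. Attribution by someone who knows the arm is therefore the likelier reading, but it is an inference.

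5. **Where the rule does not matter.** Secondary outcomes includes maternal mortality, placental abruption, postpartum haemorrhage, hypertensive disorders, small-for-gestational-age birth, low birth weight, preterm birth, intensive-care admission, congenital anomalies, miscarriage, stillbirth and neonatal death. None carries a relatedness condition or is limited to one arm. Statistical analysis plans risk ratios and risk differences with 95% confidence intervals for binary endpoints. For these events *a* = 1 in both arms already.

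6. **What is left.** The weakness covers events outside that list, in particular those managed in the outpatient setting, since the clinical outcomes come from inpatient records.

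**The case against.** The strongest reply is that the harms most relevant to a dietary intervention in pregnancy are already compared between arms as secondary outcomes (step 5). That stands, and it sets the limit of the point. A reader might infer that harms reporting as a whole is one-sided, or that the trial could support no safety statement. The documents do not support either.

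A second reply is that the sentence does not say other events go unrecorded, and that an article condenses a fuller protocol which may hold the forms and causality procedures. That is fair as to detail. But the condition of association is stated here, not omitted, and it is the only rule given. Followed as written, it has the effect shown.

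Third, the article does not say that an unmasked person makes the judgement. This also stands, and the point is worded accordingly. The loss of the control comparator does not depend on it.

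Fourth, reports go to the TSC while the independent committee is given audit and data-quality tasks. A reader might infer that the independent committee is barred from seeing harms. The article only assigns it no such task. For three counselling sessions averaging 30 minutes, based on published guidelines and added to standard care, the reporting route is largely a design preference.

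Finally, because "Two audits for each centre will be performed: at the midpoint and at the end of the trial", it is tempting to ask for a by-arm table of fetal loss, growth and prematurity at the midpoint. These are secondary outcomes, and the article plans no interim analysis of them. The table would also need an unmasked preparer and a wider committee remit. That is a debatable trade-off and is not part of this point.

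**Conclusion.** The concern holds in a limited form. For adverse events outside the listed maternal, fetal and neonatal outcomes, the stated rule leaves almost no control-arm data and makes the intervention-arm count depend on attribution. Such counts could not support a comparison between arms.

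The size cannot be put as a number, because the article gives no event rates and the fraction attributed is unknown. The direction is clear for the control arm (close to zero) and indeterminate for the intervention arm. The primary outcome, its test and the planned comparisons of listed secondary outcomes are unaffected.

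The conclusion rests on two assumptions: that the sentence is applied as worded, and that the fuller protocol, which is not at hand, has no broader recording rule. It does not rest on who makes the attribution, on the cited evidence about dietary harms, or on which committee receives the reports. This is an inexpensive improvement to the plan and does not threaten its main result.

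**What to change.** Replace the adverse-event sentence under Data monitoring and auditing with a rule to this effect: *Serious and unexpected adverse events will be recorded on the same form in both arms, regardless of presumed relation to the intervention. Relatedness will be assessed afterwards and entered as a separate field. These events will be reported by arm at the end of the trial, beside the safety-relevant secondary outcomes.* State who makes the relatedness assessment; someone masked to allocation is preferable where practicable.

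Sending the recorded events to the independent monitoring committee as well as to the TSC is optional.

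The cost is a little extra form filling, mainly in the control arm, and one more table in the final report. No new visit, committee or interim comparison is needed, and the sample size and primary analysis do not change.
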